#### Diagnostic evaluation

The presence of a major depression or an anxiety disorder is assessed according to the Composite International Diagnostic Interview (CIDI). The CIDI is a comprehensive, fully structured interview designed to be used by trained lay interviewers for the assessment of mental disorders according to the definitions and criteria of ICD-10 and DSM-IV. The diagnostic section of the interview is based on the World Health Organization's Composite International Diagnostic Interview [41-43].

### Statistical analyses

Descriptive statistics will be generated for the range of outcome variables, in particular to gauge whether randomization resulted in a balanced distribution of patients characteristics across the experimental conditions.

Repeated measures ANOVA will be used to determine the efficacy of intervention for continuous outcomes such as changes in HADS depression/anxiety symptom severity. Longitudinal changes over time in these variables will also be evaluation over all time points simultaneously using generalized estimating equations (GEEs). Analyses will be conducted in agreement with the intention-to-treat principle.

The economic data will be collected at baseline and follow-up and conducted as a cost utility analysis that is with health-related quality of life as the clinical endpoint. For the economic evaluation use will be made of the pertinent guidelines [39,44-46]. In other words, analyses will be conducted in agreement with the intention-to-treat principle; the societal perspective will be taken encompassing intervention costs, direct non-medical costs and indirect costs. Production losses will be economically valued using the friction cost method [47]. The time horizon will be set at one year, and therefore we will neither discount costs nor effects. Costs and effects will be analysed simultaneously, incremental cost-effectiveness ratios (ICERs) will be calculated and placed within 95% confidence intervals, 2,500 bootstrap replications of the ICERs will be projected on a cost-effectiveness plane, ICER acceptability curves will be plotted against different willingness-to-pay ceilings [48], and sensitivity analysis will be conducted as a matter of course focussing on uncertainty in the main cost-drivers. This will be done for the costs per QALY gained in a cost utility analysis.

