## Methods/Design

### Design

In this prospective randomized controlled trial in two parallel groups, patients are recruited by screening all LC and HNC patients, who visit the Department of Pulmonary Diseases or the Department of Otolaryngology and Head and Neck Surgery of the VU University Medical Center in Amsterdam, the Netherlands, for follow-up consultation at least one month after treatment, for distress using a computerized touch screen data collection system (OncoQuest) or by telephone using the Hospital Anxiety and Depression Scale (HADS). All patients who fulfil the in- and exclusion criteria are asked to participate. After stratification for tumour site (LC vs. HNC) and stage (stage I-II versus III-IV), 176 participating patients are randomly assigned to the intervention or control group. In order to assess efficacy, assessment before and after intervention takes place and at 3, 6, 9, and 12 months follow up.

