### Randomization

Randomization is conducted centrally by an independent statistician, in blocks of two, stratified for tumour site (LC vs. HNC) and stage (stage I-II vs. III-IV), because these variables have prognostic relevance and need to be distributed evenly across both conditions.

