### Sample size calculation

To demonstrate an effect size of 0.50 (based on a meta-analysis on psychological treatment in mild depression), 66 patients are needed in each group (power 80%, significance level 5%) [49]. Taking into account a dropout of 25%, in total 176 patients will be included. With an annual intake of 450 LC and HNC patients, 30% having psychological distress, and 50% willing to cooperate, and an inclusion period of 2.5 years, feasibility of the study is guaranteed.

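### Repeated measures ANOVA is named to determine efficacy, with GEE alongside and neither called primary; unless data are imputed, the ANOVA fits poorly with intention to treat under the 25% dropout expected

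*Protocol article*

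**What the plan says.** The Statistical analyses section of the protocol article makes three statements on this point.

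- On the efficacy method: "Repeated measures ANOVA will be used to determine the efficacy of intervention for continuous outcomes such as changes in HADS depression/anxiety symptom severity".
- On a second method for the same variables: "Longitudinal changes over time in these variables will also be evaluation over all time points simultaneously using generalized estimating equations (GEEs").
- On the analysis principle: "Analyses will be conducted in agreement with the intention-to-treat principle".

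The section does not say which of the two methods carries the efficacy conclusion.

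The Design section sets six assessments: "assessment before and after intervention takes place and at 3, 6, 9, and 12 months follow up". The Sample size calculation starts from a standardised effect of 0.50 and concludes that "66 patients are needed in each group (power 80%, significance level 5%)". It then adds: "Taking into account a dropout of 25%, in total 176 patients will be included".

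**The concern.** Classical repeated measures ANOVA needs a full set of scores for each patient. Without imputation, a patient who misses one modelled visit contributes nothing, and the analysis becomes one of completers. That sits badly with intention to treat when a quarter of patients are expected to leave.

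The GEE analysis does not settle the matter. It uses partial data, but without weighting it generally needs dropout to be completely at random. That is doubtful here. The Background section reports five-year survival of 13% in lung cancer and 50% in head and neck cancer. The Intervention section moves patients to more intensive treatment on their HADS score, in one arm only, and HADS is also the primary outcome. Dropout could therefore depend on the outcome, and differently by arm.

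The validity of the efficacy estimate is at stake. With two methods named and neither called primary, it is also unclear which result decides if they disagree.

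**Working it through.** **Inputs from the protocol article.** Effect size 0.50, 66 per group, power 80%, significance level 5%, dropout 25%, total 176 (Sample size calculation); six assessments (Design); blocks of two, so 1:1 allocation and 88 per arm (Randomization). Two-sided testing is assumed, because the article does not state sidedness.

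**Step 1: the plan's own figures.**
- Normal approximation: n = 2(1.960 + 0.842)² / 0.50² = 62.8, so 63 per group. The two-sample t-test gives 63.8, so 64. The stated 66 is within two patients of this.
- Power at 66 per group: noncentrality 0.50 × √(66/2) = 2.87; power 81.4% by the t-test (81.9% by the normal approximation).
- Dropout: 2 × 66 / (1 − 0.25) = 132 / 0.75 = 176, exactly as stated.

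The sample size is sound, and its power already rests on the 132 patients expected to remain.

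**Step 2: patients at issue.** 0.25 × 176 = 44. If all six assessments enter the ANOVA, if dropout means loss before 12 months, and if nothing is imputed, those 44 leave the analysis and 132 (66 per arm) stay.

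**Step 3: possible bias.** The documents give no dropout mechanism, so this step is illustrative. Assumptions: SD 1, six visits, true effect −0.50 SD at every post-baseline visit, 25% monotone dropout, and a log-odds slope of 1 per SD where dropout depends on the score. In the first simulation, dropout depended on worsening since baseline. Visit correlation was 0.6 exchangeable (with and without a persistent individual change of SD 0.5) or first-order autoregressive at 0.7. The complete-case contrast in mean change from baseline was:

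| Dropout mechanism | Complete-case estimate | Shift from −0.50 |
|---|---|---|
| Completely at random | −0.50 | none |
| Worsening raises dropout equally in both arms | −0.43 to −0.46 | 0.04 to 0.07 towards zero |
| Worsening raises dropout in the intervention arm only | −0.61 to −0.68 | 0.11 to 0.18 away from zero |
| Opposite relation in the two arms | −0.75 to −0.89 | 0.25 to 0.39 away from zero |

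**Step 4: the alternatives.** In a second simulation, dropout depended on the previous score and the correlation was exchangeable at 0.6.
- The complete-case change contrast was almost unbiased (−0.48 to −0.50).
- Available-case means, which is what GEE with an independence working correlation gives, were −0.50 under random dropout and −0.48 to −0.69 otherwise.
- A likelihood-type analysis of all observed scores, valid under missing at random, gave −0.50 under every mechanism tested.

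**The case against.** The strongest reply is that the article never says incomplete patients are deleted. Imputation rules may sit in a full protocol or analysis plan that is not shown, and their absence from an article is no fault. That stands, so the conflict with intention to treat is probable and not explicit. What remains is a stated choice: a method that is complete-case in its classical form, next to a 25% dropout figure.

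Second, GEE is planned for the same variables, so early scores of dropouts are not lost to the plan. This also stands, subject to the limit shown in Step 4.

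Third, the article attaches the use of all time points to GEE and ties the ANOVA only to changes in HADS. If the ANOVA compares just two assessments, fewer patients are lost and sphericity does not arise. Hence 44 is conditional on all visits entering the model.

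A reader might infer two stronger readings that the documents do not support.
- *The efficacy result is biased.* Dropout of 25% causes no bias if it is completely at random. Otherwise direction and size depend on the mechanism and on the contrast, and no passage fixes either.
- *The trial is underpowered.* The planned dropout is already allowed for. A loss appears only if completers also miss single visits, at a rate the article does not give. With an assumed 5% missed at each of five visits, 0.75 × 0.95⁵ × 88 = 51 per arm are complete. Even then, the arm-by-visit test (constant d = 0.50 after baseline, compound symmetry) has 61%, 70%, 81% or 92% power at correlations of 0.4, 0.5, 0.6 or 0.7. No shortfall can be claimed without knowing the correlation and the missed-visit rate.

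**Conclusion.** The point holds as a weakness in the stated analysis that should be fixed, short of a fatal one. The plan names two methods for the HADS variables without ranking them. The one said to determine efficacy is, unless data are imputed, a complete-case method that could set aside up to 44 of 176 randomised patients. The other generally needs dropout to be completely at random if it is unweighted. The efficacy estimate is therefore at risk of bias. Under the assumptions shown, the shift runs from none, through 0.07 SD towards zero, to 0.39 SD away from zero. These sizes are illustrative and rest on assumed correlations and dropout slopes. Stated power is unaffected by the planned dropout (about 81% at 66 per arm).

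**What to change.** In Statistical analyses, name one primary efficacy analysis: a likelihood-based linear mixed model for repeated measures on all observed HADS scores, with categorical visit and arm-by-visit terms. Put the baseline score in the outcome vector, so that every randomised patient with a baseline HADS contributes, including those with no later score. This is valid under missing at random. Keep GEE as a secondary or sensitivity analysis, labelled as such, and drop repeated measures ANOVA.

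The cost is a few sentences and slightly more modelling work. It needs standard software, no new data and no change to the sample size.

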**Methods/design:**

The study is designed as a randomized clinical trial with 2 treatment arms: a stepped care intervention programme versus care as usual. Patients treated for head and neck cancer (HNC) or lung cancer (LC) are screened for distress using OncoQuest, a computerized touchscreen system. After stratification for tumour (HNC vs. LC) and stage (stage I/II vs. III/IV), 176 distressed patients are randomly assigned to the intervention or control group. Patients in the intervention group will follow a stepped care model with 4 evidence based steps: 1. Watchful waiting, 2. Guided self-help via Internet or a booklet, 3. Problem Solving Treatment administered by a specialized nurse, and 4. Specialized psychological intervention or antidepressant medication. In the control group, patients receive care as usual which most often is a single interview or referral to specialized intervention. Primary outcome is the Hospital Anxiety and Depression Scale (HADS). Secondary outcome measures are a clinical level of depression or anxiety (CIDI), quality of life (EQ-5D, EORTC QLQ-C30, QLQ-HN35, QLQ-LC13), patient satisfaction with care (EORTC QLQ-PATSAT), and costs (health care utilization and work loss (TIC-P and PRODISQ modules)). Outcomes are evaluated before and after intervention and at 3, 6, 9 and 12 months after intervention.

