#### Care as usual

Control group patients receive care as usual, which often means a single interview by a nurse or specialised intervention delivered by a social worker, psychologist or psychiatrist. In the context of the health economic evaluation, health care uptake is closely monitored, thus allowing for detailed post-hoc description of what usual care entailed exactly.

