The economic evaluation will be conducted as a cost-utility analysis were outcomes are (changes in) health-related quality of life at patient level. Health-related quality of life is assessed with the EQ-5D [36,37] at baseline and 12 months follow-up. Direct medical and direct non-medical cost data are collected with the TIC-P [38], a widely used health service receipt interview in economic evaluations. Unit resource use (GP visits, hospital days, etc.) will be multiplied by their appropriate integral cost prices [39]. Indirect non-medical cost data related to production losses through work loss days and work cutback days will be sampled with the appropriate PRODISQ modules [40].

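### The list of costs for the cost-utility analysis omits direct medical costs, which the same protocol collects, prices and names as an outcome

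*Protocol article*

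**What the plan says.** Four places in the protocol article bear on which costs are analysed.

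- **Statistical analyses.** For the cost-utility analysis, "the societal perspective will be taken encompassing intervention costs, direct non-medical costs and indirect costs". This is the only sentence that says which cost categories enter the analysis. The section then plans ICERs with 95% confidence intervals, bootstrap replications and acceptability curves, for costs per QALY.
- **Secondary outcomes, economic paragraph.** "Direct medical and direct non-medical cost data are collected with the TIC-P". It continues: "Unit resource use (GP visits, hospital days, etc.) will be multiplied by their appropriate integral cost prices". Production losses come from a separate instrument: "Indirect non-medical cost data related to production losses through work loss days and work cutback days will be sampled", using PRODISQ modules.
- **Abstract, Methods/design.** The cost outcome is given as "costs (health care utilization and work loss (TIC-P and PRODISQ modules".
- **Care as usual.** Usual care "often means a single interview by a nurse or specialised intervention delivered by a social worker, psychologist or psychiatrist". The section adds: "In the context of the health economic evaluation, health care uptake is closely monitored". The use it names for that monitoring is to describe afterwards what usual care consisted of.

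**The concern.** The Secondary outcomes section works with three cost categories: direct medical, direct non-medical, and indirect non-medical. The Statistical analyses section uses the same vocabulary, adds intervention costs, keeps the second and third categories and drops the first. An analyst who built the cost total from that sentence would leave out GP visits, hospital days and specialist contacts.

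The term intervention costs does not obviously fill the gap. In its ordinary sense it means the cost of delivering the stepped care programme, which arises in one arm only. The contacts that the protocol describes as usual care are health care use, and they would have no place in the list.

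At stake is whether the ICER answers the question asked. The Discussion part of the abstract presents stepped care as a way to direct patients to low-cost self-management before costly specialist services. A cost total without direct medical costs cannot show whether that happened, in either direction, and would not represent a societal perspective.

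**Working it through.** The plan gives no figure to reproduce on this point, so the check is a comparison of text followed by simple algebra.

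**Step 1. Cost categories by section**

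| Category | Abstract | Secondary outcomes | Statistical analyses |
|---|---|---|---|
| Intervention costs | not named | not named | named |
| Direct medical | named, as health care utilization | collected (TIC-P); GP visits and hospital days priced | **not named** |
| Direct non-medical | not named | collected (TIC-P) | named |
| Indirect (production losses) | named, as work loss | collected (PRODISQ) | named |

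Direct medical cost is the only category that is collected but missing from the analysis list.

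**Step 2. What the omission does to the ICER numerator**

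Write C_int for the mean cost of delivering the programme per patient in the stepped care arm. Write d(·) for the difference in mean cost, stepped care minus usual care, with programme contacts excluded from d(medical).

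- List as written: ΔC₁ = C_int + d(non-medical) + d(indirect)
- List with direct medical costs: ΔC₂ = C_int + d(medical) + d(non-medical) + d(indirect)
- Error from the omission: ΔC₁ − ΔC₂ = −d(medical)

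The QALY difference in the denominator is unchanged. The error equals the between-arm difference in direct medical costs, whatever that proves to be.

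**Step 3. Can its size or sign be found?**

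The protocol gives no unit prices, no expected volumes and no share of patients reaching each step. The following illustration uses assumed values only, in arbitrary money units, with C_int = 500 and the other two differences set to 0:

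| Assumed d(medical) | ΔC₁ (omitted) | ΔC₂ (included) |
|---|---|---|
| −1000 | 500 | 500 − 1000 = −500 |
| −500 | 500 | 500 − 500 = 0 |
| 0 | 500 | 500 + 0 = 500 |
| +500 | 500 | 500 + 500 = 1000 |

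Over this assumed range the omission can overstate the incremental cost, leave it unchanged or understate it, and the sign can change. The table shows what is algebraically possible. It does not estimate what will happen in this trial.

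**The case against.** The strongest reply is that one clause is being read as if it were the whole plan. The Secondary outcomes section does more than collect health care use: it multiplies that use by cost prices, which has little purpose unless the result is analysed. The abstract makes health care utilization part of the cost outcome. The Care as usual section ties the monitoring of uptake to the economic evaluation. The clause itself declares a societal perspective, follows a reference to guidelines that include the source cited for the cost prices, and uses a verb that need not introduce an exhaustive list. On this view a phrase was lost in a condensed article. That reading is probably correct, and it stands as an account of intent. It does not remove the contradiction, because the one sentence that sets out the cost total still disagrees with the other sections.

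A reader might infer more: that the trial plans to cost usual care at zero, and that the analysis is therefore biased against stepped care. The documents do not support either inference.

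- Zero cost for usual care follows only if the clause is read alone and as exhaustive, against the three other sections.
- Bias against stepped care requires direct medical costs to be lower in that arm, and nothing in the protocol shows this. Some of its content points the other way. The Background reports that many distressed patients do not use psychosocial care, so usual-care contacts may be few. Step 4 refers patients to a psychologist or psychiatrist, or to their physician for medication, and the protocol does not say whether those contacts count as intervention or as health care costs. If they count as health care, leaving them out could favour stepped care.

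It can also be said that a rule against double counting is operational detail that an article may leave to a fuller document. Its absence is not criticised here. It is included in the fix because adding the missing category creates a possible overlap with intervention costs.

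**Conclusion.** The concern holds as an internal contradiction. The cost list in the Statistical analyses section omits direct medical costs, while the Secondary outcomes section collects and prices them, the abstract announces them as an outcome, and the declared perspective calls for them. It is most likely a drafting omission and not a decision to disregard usual care.

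If the list were applied literally, the ICER numerator would be wrong by the between-arm difference in direct medical costs, usual-care contacts included. This rests on taking intervention costs to mean the cost of the stepped care programme only. The size and direction of the error cannot be derived from the protocol.

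Severity is moderate. The sentence states an analysis rule that is wrong as written and could alter the economic conclusion, but the economic evaluation is a secondary outcome. The HADS analysis, the randomization and the sample size are untouched, and the data needed for a correct analysis are already to be collected.

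**What to change.** In the Statistical analyses section, change the list to: intervention costs, direct medical costs, direct non-medical costs and indirect costs. State that direct medical costs are counted in both arms, and that contacts already charged as intervention cost are not counted again from the TIC-P.

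This takes one or two sentences. It needs no new data collection, since the TIC-P and the pricing step are already planned, and it can be made at any time before the economic analysis.

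### The cost-utility analysis states no adjustment for baseline EQ-5D, which carries half the weight of a one-year QALY on the two-point schedule; regression adjustment would add precision at no cost

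*Protocol article*

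**What the plan says.** All places are in the protocol article.

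- **Statistical analyses, method.** "Costs and effects will be analysed simultaneously, incremental cost-effectiveness ratios (ICERs) will be calculated and placed within 95% confidence intervals", and "2,500 bootstrap replications of the ICERs will be projected on a cost-effectiveness plane". Acceptability curves follow, and sensitivity analyses centred on the main cost drivers. The horizon is one year without discounting. No covariate is named for the economic comparison, and none is excluded.
- **Statistical analyses, endpoint and data.** "This will be done for the costs per QALY gained in a cost utility analysis". On data collection: "The economic data will be collected at baseline and follow-up". On guidance: "For the economic evaluation use will be made of the pertinent guidelines [39,44-46".
- **Secondary outcomes, EQ-5D timing.** "Health-related quality of life is assessed with the EQ-5D [36,37] at baseline and 12 months follow-up".
- **Secondary outcomes, effect measure.** The cost-utility analysis is described as one whose "outcomes are (changes in) health-related quality of life at patient level".
- **Abstract, Methods/design.** EQ-5D is listed among the secondary outcomes, and then: "Outcomes are evaluated before and after intervention and at 3, 6, 9 and 12 months after intervention". That is six occasions, against two under Secondary outcomes.
- **Randomization.** Allocation is stratified by tumour site and stage, not by utility.

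**The concern.** With EQ-5D at baseline and 12 months and a one-year horizon, the area-under-the-curve QALY is the average of the two utilities. Half of each patient's effect is then a value measured before treatment. The baseline is arithmetically part of the outcome, and nothing in the design balances it between arms.

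If the arms are compared without adjustment, a chance difference in baseline utility enters the QALY difference, which is the denominator of the ICER and decides the side of the cost-effectiveness plane on which the result falls. With about 66 evaluable patients per arm, an ordinary imbalance can be as large as a plausible QALY gain. The listed sensitivity analyses are directed at costs, so none is named that would show this on the effect side.

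**Working it through.** **The plan's own sample size.** The Sample size calculation section gives an effect size of 0.50, 80% power, a 5% level and 66 per group. A two-sided t-test needs 64 per group (power 0.801; the normal approximation gives 63), and 66 gives power 0.814. Then 132 / 0.75 = 176. The figures reproduce closely, so 66 evaluable per arm is used below. The article gives no precision figure for the economic evaluation.

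**Assumptions, not in the article.** Equal EQ-5D SD *s* at all times; correlation ρ between occasions of 0.3, 0.5 or 0.7; *s* = 0.25 for absolute figures (0.20 and 0.30 as a range). The ratios below do not depend on *s* or on the number of patients.

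**Two-point raw QALY, Q = (U0 + U12)/2.**
- Unadjusted variance: s²(1 + ρ)/2.
- Covariance of Q with U0: s²(1 + ρ)/2.
- Variance adjusted for U0: s²(1 + ρ)/2 − s²(1 + ρ)²/4 = s²(1 − ρ²)/4.
- SE ratio, adjusted to unadjusted: √((1 − ρ)/2).

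**Two-point change-based QALY, (U12 − U0)/2.**
- Unadjusted variance: s²(1 − ρ)/2. The adjusted variance is the same as above.
- SE ratio: √((1 + ρ)/2).

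**About quarterly EQ-5D, raw QALY.** This simplifies the abstract's schedule by leaving out the post-intervention visit. Weights are 1/8, 1/4, 1/4, 1/4, 1/8, with equal correlations. The sum of squared weights is 2/64 + 3/16 = 0.21875.
- Unadjusted variance: s²[0.21875(1 − ρ) + ρ].
- Covariance with U0: s²(1/8 + 7ρ/8).
- At ρ = 0.5: unadjusted 0.6094 s²; adjusted 0.6094 s² − (0.5625)² s² = 0.2930 s²; SE ratio 0.693.

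| Effect measure | SE ratio at ρ = 0.3 / 0.5 / 0.7 | SE reduction |
|---|---|---|
| Two-point, raw | 0.59 / 0.50 / 0.39 | 41% / 50% / 61% |
| About quarterly, raw | 0.82 / 0.69 / 0.54 | 18% / 31% / 46% |
| Two-point, change-based | 0.81 / 0.87 / 0.92 | 19% / 13% / 8% |

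A change-based QALY on the quarterly schedule gives ratios of 0.67 / 0.78 / 0.87, so 33% / 22% / 13%. A simulation of 20,000 trials of the two-point raw case (66 per arm, ρ = 0.5) gave a ratio of 0.51 against 0.50 by formula, with both estimators centred on the true value.

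**Absolute size, two-point raw QALY, s = 0.25, 66 per arm.** The SE of the baseline utility difference is 0.25 × √(2/66) = 0.0435.
- SE of the QALY difference at ρ = 0.3 / 0.5 / 0.7: unadjusted 0.035 / 0.038 / 0.040; adjusted 0.021 / 0.019 / 0.016. At ρ = 0.5, with *s* from 0.20 to 0.30: unadjusted 0.030 to 0.045, adjusted 0.015 to 0.023.
- A one-SE baseline imbalance moves the unadjusted QALY difference by 0.0435 × (1 + ρ)/2 = 0.028 / 0.033 / 0.037. Of this, 0.0435/2 = 0.022 comes directly from the half weight and the rest through correlation with follow-up.
- The same imbalance moves a change-based QALY the other way: 0.0435 × (ρ − 1)/2 = −0.011 at ρ = 0.5.
- Illustration: an assumed 12-month utility gain of 0.05 is 0.025 QALY. At ρ = 0.5 the estimate has the wrong sign in about 25% of trials unadjusted (0.025/0.0377 = 0.66 SE) and about 9% adjusted (0.025/0.0188 = 1.33 SE).

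**The case against.** The strongest reply is that the article does not say what a reader might infer from it, namely that raw QALYs are compared without adjustment. It lists outputs (ICERs, intervals, a bootstrap, a plane, acceptability curves), and all of them can be produced from regression-adjusted increments. It cites guidelines whose content is not at hand. A journal article also commonly leaves the covariates of a secondary economic model to a fuller document. The one hint about the effect measure, the bracketed mention of changes under Secondary outcomes, points towards taking the baseline into account. All of this stands: the text is silent, and silence is not a stated choice.

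Three further inferences also fail.

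- **That precision is halved.** This holds only for raw two-point QALYs at a correlation near 0.5, and neither is fixed by the article. On the quarterly schedule the baseline weight is 1/8, and with change-based two-point QALYs the gain is modest.
- **That the ICER is biased.** Under randomisation the unadjusted QALY difference is unbiased, and the bootstrap interval reflects the extra variance. The cost is efficiency, and error given the imbalance that this one trial happens to have.
- **That costs suffer in the same way.** Baseline EQ-5D is not a component of cost, and no figure supports a gain there.

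These replies shrink the point without removing it. Under each schedule and effect measure examined, regression on baseline EQ-5D is the more precise estimator. If an unseen plan already adjusts, the remedy is only to say so.

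**Conclusion.** The point holds as a free improvement and a clarification, not as an error in the analysis. The economic analysis is specified closely, yet no step is stated for baseline utility. Followed as written, it gives a less precise QALY difference than one adjusted for baseline EQ-5D, and one that moves with chance baseline imbalance. At assumed correlations of 0.3 to 0.7 the avoidable part of the standard error is 41% to 61% (raw, two-point), 18% to 46% (raw, about quarterly) or 8% to 19% (change-based, two-point). Which range applies cannot be settled from the article, because its two EQ-5D schedules conflict and the effect measure is left open between level and change. The absolute figures and the wrong-sign rates also rest on an assumed SD and an assumed gain, and are illustrations only.

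**What to change.** In Statistical analyses, or in the analysis plan before outcomes are seen:

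1. Estimate incremental QALYs by regression on arm with baseline EQ-5D, tumour site and stage.
2. Run this regression inside each of the 2,500 bootstrap samples, resampling patients' cost-effect pairs within arm. Draw the ICER, its interval, the plane and the acceptability curves from these adjusted pairs.
3. Report the unadjusted result as a sensitivity analysis.
4. State how the QALY is constructed, and reconcile the EQ-5D schedule in the abstract (six occasions) with that under Secondary outcomes (baseline and 12 months).

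Adjusting incremental costs for baseline costs is optional; its benefit is not quantified here. The change costs a sentence or two and a few lines of code. It needs no new data, visits or patients.

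### The only interval named for the economic result is a 95% confidence interval on the ICER, which is hard to interpret if the QALY difference is near zero or stepped care saves costs (minor)

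*Protocol article*

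**What the plan says.** The Statistical analyses section of the protocol article describes a cost-utility analysis from the societal perspective. It states that "incremental cost-effectiveness ratios (ICERs) will be calculated and placed within 95% confidence intervals", then that "2,500 bootstrap replications of the ICERs will be projected on a cost-effectiveness plane" and that "ICER acceptability curves will be plotted against different willingness-to-pay ceilings", followed by sensitivity analysis. The outcome is fixed by "This will be done for the costs per QALY gained in a cost utility analysis". No method for the ICER interval is named. Neither an interval for incremental costs or incremental QALYs nor net monetary benefit is mentioned.

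Three other statements bear on the point:

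- Secondary outcomes: "Health-related quality of life is assessed with the EQ-5D [36,37] at baseline and 12 months follow-up". Under Statistical analyses, "The time horizon will be set at one year".
- Sample size calculation: 66 per group, or 176 in total after 25% dropout, for an effect size of 0.50. That figure comes from a meta-analysis of psychological treatment in mild depression, not from QALYs or costs.
- The Abstract and the Discussion both present better patient health together with lower cost as the expected benefit of stepped care.

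**The concern.** The ICER is the cost difference divided by the QALY difference. It loses the sign of each part and is discontinuous where the QALY difference is zero. Two difficulties follow for any interval expressed as ratio limits.

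First, a programme that is better and cheaper (dominant) and one that is worse and dearer (dominated) can have the same negative ICER. Positive ICERs likewise mix the better-and-dearer and worse-and-cheaper quadrants.

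Second, negative ICERs cannot be ranked. A more negative value can mean a larger saving, which is good, or a smaller health gain, which is bad. This holds even when nearly every replicate is dominant.

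What is at stake is how the economic result is read. Cost reduction is a stated purpose of stepped care, and the Discussion ties positive results to national implementation and guideline advice. A reader who takes up the ICER interval alone could draw the wrong conclusion from it or none.

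**Working it through.** **The plan's own figure.** Comparing two means with d = 0.50, two-sided 5% and 80% power: n = 2 × (1.960 + 0.842)² / 0.50² = 62.8, so 63 per arm, or 64 by the t-test. The plan's 66 is within 2 of this. 66 / 0.75 = 88 per arm, 176 in total. The sample size reproduces, but it says nothing about QALYs or costs.

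**Same ratio, opposite results.** (-500) / (+0.03) = -16,667 and (+500) / (-0.03) = -16,667. Reversing both signs leaves every ratio unchanged, so the two cases have the same ICER distribution and the same interval.

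**Size of that interval.** Assumptions, none from the documents: 66 per arm, QALY SD 0.20, cost SD EUR 8,000, correlation -0.2, bivariate normal replicates.

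- SE of QALY difference = 0.20 × √(2/66) = 0.0348. SE of cost difference = 8,000 × √(2/66) = 1,393.
- Share of replicates with a negative QALY difference = Φ(-gain / 0.0348): 28% for a gain of 0.02, 19% for 0.03, 7.5% for 0.05.
- Dominant case (+0.03, -500): 27% better and dearer, 54% dominant, 10% worse and cheaper, 9% dominated. The 2.5% and 97.5% points of the ICER are about -360,000 and +340,000, and the dominated case gives the same up to simulation error.
- Net monetary benefit at EUR 20,000 per QALY: 20,000 × 0.03 + 500 = +1,100, against -1,100. SE = √(696² + 1,393² + 2 × 0.2 × 696 × 1,393) = 1,677. The 95% intervals are about -2,190 to 4,390 and -4,390 to 2,190. The share of replicates with positive net benefit is Φ(1,100 / 1,677) = 74%, against 26%.

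**No order among negative ratios.** From +0.03 QALY and -500, doubling the saving gives -1,000 / 0.03 = -33,333. Halving the health gain gives -500 / 0.015 = -33,333. The first is better than the starting point and the second is worse. With +0.10 QALY and -4,000 (correlation 0), more than 99% of replicates are dominant and the percentile interval is roughly -135,000 to -11,000. Neither end can be called the favourable one.

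**How likely is spread over four quadrants?** Differences are in SD units, SE = √(2/66) = 0.174, correlation 0. The first four columns take the stated difference as observed. The last takes it as true and gives the chance, over repeated trials, that every quadrant holds at least 1% of replicates.

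| QALY / cost difference | Better, dearer | Dominant | Worse, cheaper | Dominated | All four ≥ 1% |
|---|---|---|---|---|---|
| 0 / 0 | 25% | 25% | 25% | 25% | 83% |
| 0.2 / 0 | 43.7% | 43.7% | 6.3% | 6.3% | 64% |
| 0.2 / -0.2 | 11.0% | 76.5% | 11.0% | 1.6% | 48% |
| 0.3 / 0 | 47.9% | 47.9% | 2.1% | 2.1% | 45% |
| 0.5 / 0 | 49.9% | 49.9% | 0.1% | 0.1% | 12% |
| 0.5 / -0.5 | 0.2% | 99.6% | 0.2% | 0.0% | 1% |

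**Is a difference of 0.2 to 0.3 SD plausible?** Assume QALYs are the straight-line area between the two EQ-5D measurements, with no baseline adjustment. A utility gain of 0.50 SD at 12 months then becomes 0.25 / √((1 + r)/2) SD in QALYs, where r is the correlation between baseline and 12 months: 0.31 for r = 0.3 and 0.27 for r = 0.7. Baseline adjustment would remove this attenuation.

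**The case against.** A reader might infer that with this sample the replicates are bound to fall in all four quadrants. The documents do not support that. They give no QALY or cost difference and no SD, and the last column of the table runs from 83% down to 1% depending on what is assumed.

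A reader might also infer that the plan cannot tell a dominant programme from a dominated one. That is wrong for the plan as a whole. The plane shows directly where the replicates lie. Acceptability curves built in the usual way from net benefit would give 74% against 26% in the example. The sentence lists these outputs side by side and does not make the ICER interval the decisive one.

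The plan does not say that the interval will be cut from sorted ratios, and an article may leave that method to the fuller document, so its absence is not counted here. The sign argument does not depend on the method: Fieller's inequality is also unchanged when both differences change sign, and no method gives negative ratios an order of merit.

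Finally, the net-benefit intervals in the example both include zero and overlap heavily. They do not prove one programme better than the other. Their advantage is that the scale has a direction. The objection therefore removes the strong readings and lowers the severity, but does not make the ICER interval a good summary.

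**Conclusion.** The point holds in a limited form. The one interval named for the economic result is on a scale where opposite results share a value and where values in the quadrant the authors hope for cannot be ranked. Both facts are algebra and need no assumption. How much this matters in the actual data cannot be known from the documents. At 66 per arm, appreciable spread over four quadrants is a realistic prospect for differences up to about 0.2 to 0.3 SD and unlikely for 0.5 SD in both costs and QALYs. The euro figures rest entirely on the assumed SDs and correlation. The economic evaluation is a secondary outcome and the plane and curves carry the needed information, so this is a minor improvement to reporting.

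**What to change.** In the economic paragraph of Statistical analyses, replace the confidence interval on the ICER with the following, all from the same 2,500 replicates:

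- 95% intervals for incremental costs, for incremental QALYs, and for incremental net monetary benefit at the willingness-to-pay ceilings used for the acceptability curves;
- the share of replicates in each of the four quadrants;
- the ICER as a point estimate, with an interval only if essentially all replicates lie in a single quadrant where the ratio can be ordered (better and dearer, or worse and cheaper).

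Keep the plane and acceptability curves. The change is a sentence or two, with no new data and no further bootstrap. The one downside is that net benefit must be quoted at stated ceilings, so these need to be named.
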